#### Recruitment

Women will be recruited de facto by being under the care of a participating health service. Women always have an option to decline testing and, if GDM is diagnosed, to decline treatment. Informed consent will not be requested beyond the routine invitation to opt out of the SPR and the option at any time to refuse any aspect of management.

#### Randomisation

As the expected number of births varies across the participating centres, a stratified randomisation by centre size was conducted using two strata. The first strata was the two largest populated study centres (Stockholm and Gothenburg) which was randomised to change GDM criteria in June or August of 2018. The second strata with the nine remaining centres was changing, one centre per month, in a randomised order from February to July and September to November of 2018. The randomisation allocation was performed using computer-generated, random allocation sequences using SPSS version 22 (Armonk, NY:IBM Corp) by the study statistician at Clinical Epidemiology and Biostatistics, Region Örebro County. The randomisation was concealed from the participating centre and the list is stored in a safe at Örebro University Hospital.

The study statistician provided information on the randomisation to the study coordinator who in turn informed the relevant centre through the local PI, 2 months prior to when the centre being randomised to using the new GDM criteria. Staff at all sites were blinded until informed by their local PI of their start date to change from the *control period* (old GDM criteria) to the *intervention period (*new GDM criteria*)*.

#### Monitoring of adhesion to the study protocol

Every month each centre reported their monitoring according to a checklist on the website (ref according to guidelines) to make sure that the guidelines for the CDC4G study (e.g. GDM treatment, blood sampling methods, obstetric surveillance, switch to the new criteria) were followed every step of the study. In addition, the number of women with GDM diagnosed every month during the study period is registered. Severe possible adverse outcomes such as (severe maternal hypoglycaemia (low blood glucose levels that requires assistance from another person to treat) and lactic acidosis in metformin treated women) is reported each month. Interim analysis is performed by the study coordinator every month to identify any safety or protocol breaches. The study data and safety monitoring board (DSMB) is available to determine whether any safety issues warranted termination of the trial.

#### Procedures

A 3-month *national preparation period* was organized between October to December 2017 (Fig. 2), for all sites to consolidate their local approach to screening, changing diagnostic testing to venous sampling, modifying and consolidating the agreed approach to GDM treatment and the agreed approach to obstetric management.

The trial started on the 1st of January 2018 with 1 month of baseline data collection when no randomisation occurred. Subsequently, at periodic time points called “steps”, sites changed to the new GDM criteria in a randomised order over a 10 months period. In December 2018 all sites used the new criteria. The last birth is expected in August 2019.

##### Booking screening

Booking screening varied between the centres. In some centres, high risk women underwent an OGTT, other centres used universal random blood glucose screening to identify those for referral to OGTT, see Table 1. The OGTT thresholds used for overt diabetes in pregnancy are listed in Table 1.

##### The oral glucose tolerance test (OGTT)

Throughout the study period, a 2-h 75 g OGTT was undertaken following booking screening, at 24–29 weeks gestation or if there was a clinical indication (e.g. polyhydramnios, accelerated growth or high random blood glucose).

Venous sampling were used with glucose measurements performed either by the local laboratory or with point of care testing (Table 1). All the laboratories are accredited according to SS-EN-ISO/IEC 15189. As part of the accreditation the laboratories participate in inter-laboratory comparison schemes either from Equalis (https://www.equalis.se/en/) or in schemes organised by the local hospital organisation.

##### GDM management guidelines

GDM management (treatment and obstetrical surveillance) was the same in all centres before and after the switch. All women received a GDM information leaflet and written dietary advice in Swedish and translated into five other languages (English, Pashto, Somali, Arabic and Dari). All women diagnosed with GDM were offered lifestyle advice from a registered dietitian. Further general GDM information was provided by the midwife if lifestyle treated, and the diabetes team if treated with insulin or metformin. A local diabetes nurse or trained midwife taught women on how to undertake self-measurement of plasma glucose (SMPG). Different meters were used, but all were capable of uploading data through DIASEND® (Glooko AB, Göteborg, Sweden) which is considered to be part of the local clinical records. SMPG was recommended to occur four times per day: Fasting and 1 h after breakfast, lunch and dinner among those who are lifestyle treated and seven times per day among those treated with insulin and/or metformin (before and 1 h after meals and at night before bed).

Target values for capillary plasma glucose were < 5.3 mmol/L fasting (before breakfast), < 6.0 mmol/L before other meals, < 8.0 mmol/L 1 h after meals, and < 7.0 mmol/L before bedtime. Those with three or more values above target during 1 week were commenced on pharmacological treatment or intensified treatment if already on metformin/insulin. GDM management (treatment and obstetrical surveillance) was the same in all centres before and after the switch.

### Pharmacological treatment

Metformin is accepted for treatment of GDM by the Swedish National Board of Health (https://www.socialstyrelsen.se/globalassets/sharepoint-dokument/artikelkatalog/nationella-riktlinjer/2015-4-12.pdf) and it is used mainly for overweight patients (BMI ≥ 25 kg/m^2^), especially where fasting glucose and basal glucose levels were elevated during the day. Written and oral information was provided regarding adverse effects and that metformin crosses the placenta. Start dose was 500 mg once daily, with increasing one tablet every third day until target glucose level was achieved.

Insulin is recommended when metformin is not expected to bring hyperglycaemia rapidly under control, or when considered inappropriate for clinical reasons or declined by the patient. If fasting blood glucose is above the target, intermediate acting insulin (NPH) is the first line of choice. Long acting analogue insulins are considered if the blood glucose targets are not reached. Rapid acting insulin analogues are used to manage elevated postprandial glucose levels. Evaluation of glucose values and titration of insulin dose are recommended twice a week initially, after which titration is performed once a week. Changes in insulin doses occurred if three or four values are above the target value over a 1-week period. Starting doses are 4–8 units depending on the glycaemia and other clinical factors (e.g. BMI).

### Obstetric surveillance

All women with GDM receive written information about health and exercise and continue with the usual obstetric/midwifery care including additional intervention when indicated. Women with diagnosed GDM and lifestyle management alone received expectant care as per normal pregnancy management with foetal weight estimation at week 38 for pre-delivery assessment. For women receiving metformin or insulin treatment, additional ultrasound assessments for foetal weight estimation was performed at least 2 times during pregnancy: at weeks 28–32 and latest at 38 weeks. Induction occurs if not delivered before 40 + 6 for medically treated GDM women, and for diet treated GDM induction at the latest 42 + 0.

### Data collection

Data will be collected through the SPR, a national quality registry [33]. An additional electronic case record form is created with manually entered data not otherwise collected in the SPR (e.g. neonatal blood glucose and repeat OGTT values). Follow up studies will use the National Diabetes Register (NDR) and other Swedish health care registers (SNQ, Prescribed Drug register, Statistics Sweden). Glucose monitoring and target adherence were collected through the use of DIASEND®.

First data set extraction is planned to be completed during 2020. The project coordinator and steering group will have access to the complete dataset when available.

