Internationally, the prevalence of GDM varies from 1 to 28% depending on the ethnic composition and prevalence of T2DM of the background population, local GDM screening strategies and diagnostic criteria [15–17]. This variation in screening and diagnostic approaches has made global comparisons of GDM prevalence and outcomes problematic. In order to progress towards a universal standard approach to GDM diagnosis, the World Health Organisation (WHO) recommended in 2013 that a 2-h 75 g oral glucose tolerance test (OGTT) should be used, with three time points blood testing (fasting, 1- and 2-h) [1]. These 2013 WHO criteria define GDM as ≥5.1, ≥10.0 and/or ≥ 8.5 mmol/L fasting, 1-h and/or 2-h thresholds. These cut-off values are based on a ≥ 75% adjusted excess risk of adverse neonatal outcomes (e.g. large for gestational age (LGA), foetal hyperinsulinemia), based on data from the Hyperglycaemia and Adverse Pregnancy Outcomes (HAPO) study involving 25,505 women from nine countries [18]. There has been debate over the merits of these new criteria as the number of women diagnosed with GDM would be expected to increase by 15–30%, raising concerns over their cost and clinical effectiveness [19–22]. While the thresholds are based upon calculated excess risk, the decision to base the diagnostic criteria on ≥75% excess risk was based upon consensus. Some countries (e.g. Canada, Norway) have reduced GDM numbers by using thresholds based upon a ≥ 100% excess risk of adverse neonatal outcomes (5.3- and/or 10.6- and/or 9.0 mmol/L, respectively) [23, 24]. Others have not based their criteria on HAPO data at all (e.g. England, New Zealand).

Older Swedish GDM criteria are based on varying cut-off values. If a fasting threshold was used (not used in one region), then ≥7.0 mmol/L was considered GDM. The 2 h criteria ranged from 9.0–11.1 mmol/L, using either capillary or venous samples. Using these criteria, 1–3% of the 115, 000 births were complicated by GDM annually. In June 2015, following a review of the available evidence, the Swedish National Board of Health and Welfare (SNBHW) recommended a move to the 2013 WHO diagnostic criteria, using venous sampling. The SNBHW made no recommendations in relation to the screening (e.g. universal vs risk factor).

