## Methods

### Study design

The Changing Diagnostic Criteria for Gestational diabetes (CDC4G) in Sweden study is a national prospective, unblinded, SW-CRCT of the switch from the former Swedish diagnostic criteria to the WHO 2013 criteria for GDM i.e. to the 3 point OGTT with fasting plasma glucose, 1-h and/or 2-h diagnostic thresholds of ≥5.1, ≥10.0, ≥8.5 mmol/L, respectively (Fig. 1). Each participating centre constitutes one cluster, in which the patients continue to undergo screening for GDM following their usual approach, see Table 1. The time of transition to the new criteria is randomised and subsequently rolled out until all 11 clusters (i.e. centres) implement the new GDM regimes during 2018, see Fig. 2. The transition necessitated the introduction of a fasting glucose sample in one region, and a 1-h sample across all 11 regions. This means that a total population evaluation of the change is required, as many women with GDM diagnosed by the new criteria, will not be identified during the control period (e.g. those without the 1-h test). A sub-analysis among those with untreated and treated GDM by the WHO 2013 is also planned.

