#### Outcomes

The primary outcome is LGA (birth weight above the 90th percentile for gestational age and sex using centile tables) based on Swedish reference population (twins, major malformations and intrauterine deaths excluded from reference population). This is the only common pregnancy outcome shown to be substantially and consistently reduced by treating GDM [32].

Secondary outcomes for neonate and mother are listed in Table 2.

**Table 2 Tab2:** Outcomes, sampling and measurements

			Data collection points		
	Method	Sources	Baseline	During pregnancy	Birth/postpartum
Primary Outcome					
LGA^a^	scale	SPR^b^			x
Secondary maternal outcomes					
Gestational Hypertension	Blood pressure or ICD code	SPR^b^/ eCRF^f^		x	x
Pre-eclampsia	ICD code	SPR^b^		x	x
Shoulder dystocia	ICD code	SPR^b^			x
Induction of labour	ICD code	SPR^b^			x
Emergency LSCS	ICD code	SPR^b^			x
Elective LSCS	ICD code	SPR^b^			x
Instrumental delivery	ICD code	SPR^b^			x
Length of maternal stay from delivery to discharge	hours, days	SPR^b^			x
Perineal trauma-3 and 4 degree	ICD code	SPR^b^			x
Breastfeeding at hospital discharge	Yes/no	SPR^b^			x
Maternal HbA1c (mmol/mol)	Blood sample	eCRF^f^	x	x	
Self-reported health	Scale 1–6	SPR^b^		x	x
Satisfaction with childbirth	Scale 1–10	SPR^b^			x
Post-part bleeding	ml	SPR^b^			x
Gestational weight gain	g or kg	SPR^b^	x	x	
Secondary neonatal outcomes					
Stillbirth (≥22 + 0)	ICD code	SPR^b^/SNQ^c^			x
Neonatal death (< 28 days)	ICD code	SPR^b^ /SCB^d^			x
Erbs palsy	ICD code	SPR^b^/SNQ^c^			x
Metabolic acidosis^g^	Umbilical artery and venous blood sample	SPR^b^			x
1,5,10 min Apgar score < 4	Clinical examination	SPR^b^			x
Hypoxic ischemic encephalopathy I-III	ICD code	SPR^b^/SNQ^e^			x
Intracranial haemorrhage	ICD code	SPR^b^/SNQ^e^			x
Meconium aspiration syndrome	ICD code	SPR^b^/SNQ^e^			x
Mechanical ventilation		SPR^b^/SNQ^e^			x
Fractured clavicle/humerus	ICD code	SPR^b^/SNQ^e^			x
Blood glucose in the infants (mmol/L)	Blood sample	eCFR^f^			x
Preterm birth < 37, 34 or 32 weeks	ICD code	SPR^b^			x
NICU date	(xxxx/yy/zz)	eCRF^f^			x
NICU days	days	eCRF^f^/SPR^b^			x
SGA^h^	Calculated from birth weight / gestational age/gender	SPR^b^			x
Bilirubin (highest value)	Blood sample	eCRF^f^			x
Phototherapy	Medical record	eCRF^f^			
Hypoglycaemia needing IV therapy		eCRF^f^			x
Supplementary feeding					
Supplementary feeding indication	Medical record	eCFR^f^			x
Interval (hours) and volume (ml) of supplementary feeding		eCFR^f^			x

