As the randomisation is on the cluster level and not on the participant level, we will adjust for important prognostic predictors for LGA, such as chronic hypertension, mother’s age, BMI, country of mother’s birth and the mother’s smoking behaviour during pregnancy. Stratification with interaction tests by prognostic factors will be used to further investigate if the associations with LGA between the two diagnostic criteria are heterogeneous and the new diagnostic criteria have an even larger impact in some subgroups according to risk factors.

Because of the stepped wedge study design, some recommended design-specific analyses will be conducted such as stratification by time period to evaluate if the intervention association with outcomes are homogenous during the study time period, or heterogeneity within centres between the two interventions. The secondary adverse neonatal and maternal outcomes will be analysed using the same type of methods and considerations as for the primary outcome. A sub-analysis will be conducted comparing those with fasting glucose 5.1–6.9 mmol/L and/or 2-h glucose 8.5–8.9 mmol/L before and after the switch in criteria.

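### Several eCRF-only secondary outcomes are to be compared like LGA, although their ascertainment may shift with the GDM label that the switch itself changes

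*Protocol article*

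**What the plan says.** All references are to the protocol article.

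- **Source of the data.** Under Data collection, the eCRF is the place for "manually entered data not otherwise collected in the SPR (e.g. neonatal blood glucose and repeat OGTT values". Table 2 gives the eCRF as the only source for "Blood glucose in the infants (mmol/L", highest bilirubin, phototherapy, "Hypoglycaemia needing IV therapy", the supplementary-feeding and dextrose-gel items, maternal HbA1c and NICU date. NICU days can also come from the SPR. LGA comes from the SPR.
- **Analysis.** Statistics and data analysis states: "The secondary adverse neonatal and maternal outcomes will be analysed using the same type of methods and considerations as for the primary outcome". It makes no exception for eCRF items.
- **Effect of the switch on the label.** Study design states that "many women with GDM diagnosed by the new criteria, will not be identified during the control period" and concludes that "a total population evaluation of the change is required". The same section describes the trial as unblinded.
- **Not stated.** The article does not say in which infants glucose or bilirubin is measured, whether a maternal GDM diagnosis leads to the measurement, or for which women the eCRF is completed. The only incompleteness it anticipates (about 10%) concerns maternal characteristics, mainly BMI.

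**The concern.** The authors recognise that a diagnosis-based comparison would be distorted, because the intervention redefines the diagnosis, and they answer this by evaluating the whole population. That answer works for LGA, which is taken from the SPR whatever the mother's diagnosis. It works for a hand-entered laboratory value or treatment item only if that item is measured and entered without regard to the diagnosis.

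If measurement or entry follows the label, the measured set changes at each centre on its own switch date. That change has the same pattern over centre and time as the intervention indicator. Centre effects, calendar-time effects and adjustment for maternal characteristics therefore cannot separate it from a treatment effect. More recorded neonatal hypoglycaemia after the switch could mean only more testing. A lower rate among tested infants could mean only that milder cases have joined the tested group. Both bear on the article's aim of testing whether adverse neonatal outcomes fall.

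**Working it through.** **The plan's own figure.** The only calculation in the article is for LGA: 47,916 women, 11 centres, ICC 0.0026, 90% power, 5% significance, 10% to 8.5%. It reproduces as 11 centres × 12 periods × 363 women = 47,916. The Hussey–Hughes variance, assuming one centre switching per period and a two-sided test, is

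var = Iσ²(σ² + Tτ²) / [(IU − W)σ² + (U² + ITU − TW − IV)τ²],

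with I = 11, T = 12, U = 66, W = V = 506, σ² = 0.09/363 and τ² = 0.09 × 0.0026/0.9974. The standard error is 0.00463 and the power Φ(0.015/0.00463 − 1.96) = 0.90. Nothing below changes this. The article gives no figure for the eCRF outcomes.

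**Illustration for events counted per birth.** Let g be the share of mothers labelled GDM, and tG and tN the probabilities that an infant of a labelled or unlabelled mother is tested and entered. Suppose the true risk is the same in all infants and is not changed by the switch. The recorded-event ratio, after versus before, is then

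R = [g₁tG + (1 − g₁)tN] / [g₀tG + (1 − g₀)tN].

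Inputs from the Background section: "1–3% of the 115, 000 births were complicated by GDM annually" under the old criteria, and an expected 15–30% increase in diagnoses. The increase is read here as relative, which the article does not specify. All values of tG and tN, and the larger prevalence shifts, are assumptions.

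| GDM before → after | tG = 1, tN = 0.10 | tG = 1, tN = 0.05 | tG = 0.9, tN = 0.20 |
|---|---|---|---|
| 2% → 2.3% (relative 15%) | 0.1207/0.1180 = 1.02 | 0.07185/0.0690 = 1.04 | 0.2161/0.2140 = 1.01 |
| 2% → 2.6% (relative 30%) | 0.1234/0.1180 = 1.05 | 0.0747/0.0690 = 1.08 | 0.2182/0.2140 = 1.02 |
| 1% → 3% | 0.127/0.109 = 1.17 | 0.0785/0.0595 = 1.32 | 1.07 |
| 2% → 5% | 0.145/0.118 = 1.23 | 0.0975/0.0690 = 1.41 | 1.10 |
| 3% → 10% | 0.190/0.127 = 1.50 | 0.145/0.0785 = 1.85 | 1.22 |

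If tG = tN, then R = 1.00 in every row.

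**Illustration for rates among tested infants.** Take the extreme in which only infants of labelled mothers are tested. Diagnoses rise by a fraction k, and newly tested infants carry relative risk r.

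- Events per birth change by 1 + kr.
- The rate among tested infants changes by (1 + kr)/(1 + k).

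With r = 0.5, events per birth rise by factors of 1.075 (k = 0.15) and 1.15 (k = 0.30). The rate among tested infants falls by factors of 1.075/1.15 = 0.935 and 1.15/1.30 = 0.885. With r = 1, events per birth rise by 1.15 to 1.30 and the rate among tested infants does not change. The apparent direction therefore depends on the denominator and on r.

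**The case against.** A reader might infer that a GDM label prompts neonatal testing in these centres. The article does not say so. Manual entry alone does not show it, and listing infant glucose beside repeat OGTT values is at most suggestive. That objection stands, and the point can only be conditional.

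Testing rules and eCRF completion rules usually sit in a full protocol or manual that is not shown, so their absence here is no fault. That also stands. What remains is something the article does fix: a comparison of the secondary adverse outcomes on the LGA pattern, with no condition on how they are ascertained.

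The analysis sentence can also be read as naming a model family rather than an all-births denominator, and some feeding items are hardly adverse outcomes. This is fair in part, but either denominator is exposed: all births to inflation, tested infants to dilution.

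The planned sub-analysis selects women by glucose value rather than by label. It gives no protection here, because many of those women would be unlabelled before the switch and labelled after it.

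Two further inferences are not supported. One is that the cost analysis is affected: the article takes utilisation and self-rated health from the SPR and names no eCRF item as a cost input. The other is that IV-treated hypoglycaemia and NICU admission are safe comparators because a neonatal register covers them. Table 2 gives IV-treated hypoglycaemia and NICU date the eCRF only, the article states no all-birth register source for them, and both could themselves depend partly on detection.

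**Conclusion.** The point holds conditionally and should be addressed. For outcomes sourced only from the eCRF, the stated LGA-type comparison is interpretable only if measurement and entry do not depend on the maternal GDM label, and the article neither says this nor makes the comparison depend on it. If there is no dependence, the bias is nil. With all labelled and 5–10% of unlabelled infants tested (assumed), the spurious ratio is about 1.02–1.08 for a relative 15–30% rise from 2%, and 1.17–1.85 for the larger assumed prevalence shifts. Weaker dependence gives smaller values.

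The concern is strongest for measured infant glucose. It is less direct for bilirubin, and only partial for phototherapy and IV-treated hypoglycaemia, which are treatment events. LGA, the sample size and the SPR-based cost analysis are not affected.

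**What to change.** In Statistics and data analysis, replace the unconditional sentence on secondary outcomes with three rules.

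1. Tabulate, for each eCRF outcome, the proportion of all births with the item measured and the proportion with it entered, by centre and month and before versus after the switch.
2. Keep the LGA-type comparison only for outcomes ascertained independently of the maternal GDM label, with all births as denominator. Treat IV-treated hypoglycaemia and the eCRF-only NICU items as comparable only if a source covering all births is confirmed.
3. Report the remaining eCRF measurements descriptively, with no comparative claim.

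If measurement and entry do cover all births regardless of label, one sentence saying so, supported by the table, settles the matter.

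The cost is one extra table, and possibly fewer secondary outcomes carrying a comparative claim. Nothing changes in the conduct of the trial, the primary analysis or the sample size.
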